## STATISTICAL ANALYSIS PLAN

### Hypotheses for primary outcome measures

**Hypothesis 1:** Quality of dying of residents as evaluated by staff is better in facilities using the 'PACE Steps to Success' palliative care programme than facilities which provide care as usual compared to baseline.

**Hypothesis 2:** Staff attitudes and knowledge towards palliative care are better in facilities using the 'PACE Steps to Success' palliative care programme than facilities which provide care as usual compared to baseline.

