### Primary outcome measures

**Hypothesis 1:** Quality of dying of residents

The outcome measures to test hypotheses 1 include several aspects of quality of dying of the residents of the participating long-term care facilities (LTCFs).

- End-of-Life in Dementia – Comfort Assessment in Dying (EOLD – CAD)
  - Comfort during the last 7 days of life
  - Answered by the staff most involved in care and the most closely involved relative of the deceased resident at baseline, month 13 (T1), and 17 (T2)
- Quality of Dying in Long-Term Care (QOD – LTC):
  - Quality of dying in long-term care
  - Answered by the staff most involved in care for the deceased resident at baseline, month 13 (T1) and 17 (T2)

**Hypothesis 2:** Staff attitudes and knowledge towards palliative care

The outcome measures to test hypotheses 2 include several aspects of the attitudes and knowledge towards palliative care of staff in the participating LTCFs. These outcome measures were answered by all care staff present in participating LTCFs during data collection at baseline and month 12.

- End-of-Life Professional Caregiver Survey (ECPS)
  - Staff attitudes towards patient and family communication, cultural, and ethical values
- Palliative Care Survey (PCS)
  - Staff knowledge on palliative care
- Self-Efficacy in End-of-Life Care Survey (S-EOLC)
  - Staff confidence in communicating with residents and families about end-of-life (i.e. self-efficacy)

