**Sample**

**Hypothesis 1:** To test hypotheses 1, all deceased residents for whom the staff most involved in care for the deceased resident completed a questionnaire will be included in the sample.

**Hypothesis 2:** To test hypotheses 2, all care staff present in participating LTCFs during data collection, who completed a questionnaire regarding their attitudes and knowledge towards palliative care, will be included in the sample.

**Hypothesis 3:** To test hypotheses 3, all deceased residents for whom the most closely involved relative of the deceased resident completed a questionnaire will be included in the sample.

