## **Data analyses**

### **Step 1.** Exploring the data and data assumptions

The nature of each variable, as well as the influence of certain data assumptions on the study results must be explored prior to primary data analyses.

**Step 1.1.** Explore the number of cases in T1 and T2 to determine statistical power for each post intervention measurements. T1 and T2 can be used separately for the analysis when statistical power is at least 80%.

**Step 1.2.** Due to potential turn-over of staffs in LTCFs, the samples – care staffs present in participating LTCFs during data collection– with both the baseline and post-intervention measurements will be explored.

**Step 1.3.** Check data assumptions for regression analyses.

**Normality of distribution** – For continuous variables, a graphical representation (histogram) or the Shapiro Wilk-test or Kolmogorov Smirnov test can be used to check for normality of the distribution. If the normality of distribution is violated, log-transformation may for example be done. The partner responsible for conducting the analysis would need to discuss in the consortium on how skewed data can further be used for the analysis.

**Linearity** – Linearity between the outcome measures and the intervention variable or covariates will be checked through visual inspection of the scatter diagram. If the assumption of linearity is violated, the partner responsible for conducting the analysis would need to discuss in the consortium on how these data can be further used for the analysis – e.g. transforming into quartiles.

**Step 1.4.** Prepare the variables to be used for the data analyses based on the exploration of data and data assumptions.

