All analyses will be two-tailed and considered significant if  $\alpha = 0.05$ . In addition, data will be analysed by using statistical software program suitable for the necessary statistical analyses, such as multilevel mixed model analysis and multiple imputation – e.g. STATA, SAS, or IBM SPSS.

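### Five primary scales are each tested at two-sided 0.05 with no multiplicity or success rule, and a conditional T1/T2 split can raise the number of primary tests to seven

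*Combined protocol and SAP*

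**What the plan says.** There are two primary hypotheses. H1 reads "Quality of dying of residents as evaluated by staff is better in facilities using the 'PACE Steps to Success' palliative care programme", and H2 reads "Staff attitudes and knowledge towards palliative care are better in facilities using the 'PACE Steps to Success' palliative care programme", each against usual care and relative to baseline (Hypotheses for primary outcome measures).

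The section Primary outcome measures places two scales under H1 (EOLD-CAD and QOD-LTC, at baseline, month 13 = T1 and month 17 = T2). It places three under H2 (ECPS, PCS and S-EOLC, at baseline and month 12). On H2 it says: "The outcome measures to test hypotheses 2 include several aspects of the attitudes and knowledge towards palliative care of staff".

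Step 4, Regression analyses, estimates a group-by-time interaction for each outcome and closes with the significance rule: "All analyses will be two-tailed and considered significant if" α = 0.05. Nothing in the document divides that level, orders the scales, names a lead scale, or says what pattern of results would support a hypothesis.

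Step 1.1 first looks at the number of cases in each wave and then says "T1 and T2 can be used separately for the analysis when statistical power is at least 80" per cent.

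On the rater, the EOLD-CAD entry under H1 says "Answered by the staff most involved in care and the most closely involved relative of the deceased resident". The Sample section, for H1, says "all deceased residents for whom the staff most involved in care for the deceased resident completed a questionnaire will be included in the sample".

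**The concern.** With five primary tests at the full level and no success rule, a single significant scale can be reported as support for a primary hypothesis. The 5% then applies to each scale and not to the primary claim.

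The number of primary tests is also not fixed. The 80% condition needs an effect size, a standard deviation and an intracluster correlation, and the plan gives none. Whether the condition is met therefore depends on inputs chosen later. Meeting it permits a split but does not require one, and the plan does not say which wave would be primary after a split. What is at stake is how far a positive primary result from this trial can be trusted.

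**Working it through.** The plan states no overall error rate, so there is no figure to reproduce. Its one stated level, 0.05, equals the overall error only for a single test: 1 − 0.95¹ = 0.05.

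**Inputs from the plan**
- Level: 0.05 two-sided for every analysis (Step 4).
- Primary scales: 2 (H1) + 3 (H2) = 5.
- Follow-up waves: two for the resident scales, one for the staff scales. With a split, 2 × 2 + 3 = 7 tests, not 10.
- Correlations between test statistics: not given, so assumed and varied.

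**Independent tests:** error = 1 − 0.95^k.
- k = 2 (H1): 1 − 0.9025 = 9.8%
- k = 3 (H2): 1 − 0.8574 = 14.3%
- k = 5: 1 − 0.7738 = 22.6%
- k = 7: 1 − 0.6983 = 30.2%

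**Common correlation ρ**, jointly normal statistics, c = 1.96:

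error = 1 − ∫ [Φ((c − √ρ·u)/√(1−ρ)) − Φ((−c − √ρ·u)/√(1−ρ))]^k φ(u) du

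| Tests | ρ = 0 | ρ = 0.5 | ρ = 0.7 | ρ = 0.9 |
|---|---|---|---|---|
| H1, k = 2 | 9.8% | 9.1% | 8.4% | 7.0% |
| H2, k = 3 | 14.3% | 12.5% | 10.9% | 8.4% |
| All five scales | 22.6% | 18.3% | 14.8% | 10.2% |
| Seven, with split | 30.2% | 23.0% | 17.8% | 11.4% |

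For jointly normal two-sided tests, independence is the worst case, so 30.2% is an upper limit for seven tests. T1 and T2 share a baseline and are positively correlated. With a T1–T2 correlation of 0.5–0.7 and a within-hypothesis correlation of 0–0.5, simulation gives 25–29%.

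**Effect of the repair.** When no scale has an effect, Holm over five makes a false claim only if the smallest p-value is below 0.05/5 = 0.01. For independent tests that is 1 − 0.99⁵ = 4.9%, and it is at most 5% under any correlation. The number of tests has to be fixed first: seven independent tests each at 0.01 would give 1 − 0.99⁷ = 6.8%.

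**Power cost.** A scale with 80% power at 0.05 has a standardised effect of 1.960 + 0.842 = 2.802.
- At 0.025: Φ(2.802 − 2.241) = 71%
- At 0.01: Φ(2.802 − 2.576) = 59%

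**The case against.** Several objections have force.

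- **One positive scale may not be enough.** The plan does not say that it is. A rule requiring every scale of a hypothesis to be significant would remove the inflation. No such rule is written, so this limits the wording of the point but does not answer it.
- **H1 and H2 concern different populations** (residents and staff) and could be treated as separate families. That is reasonable, but each family alone still exceeds 5%.
- **Estimates, 95% confidence intervals and Cohen's d are planned for the outcomes.** This makes selective reporting harder. It does not control error.
- **The power inputs may sit elsewhere.** Section I refers to Annex I of the Grant Agreement, which is not among the documents. The complaint is therefore limited to what this plan states.

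Some stronger readings are tempting and are not supported.

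- A reader might infer that the rater of the primary endpoint is open. It is not: H1 and its sample both specify staff. The mention of relatives describes who completes EOLD-CAD, and only the role of the relative-rated version needs stating.
- A reader might infer that the follow-up window can be chosen on results. Step 1.1 looks at case numbers, not at outcomes or group differences.
- A reader might infer that a split leaves each wave underpowered. The rule permits a split only at 80% power or more, so a case where pooling gives 80% and one wave falls short is one in which the plan would not split.
- A reader might say that a split halves the data behind each test. Only the follow-up data are divided. The tested contrast is change from baseline, and the baseline part is unaffected.

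**Conclusion.** The point holds. Following the plan as written gives an overall chance of a false primary claim well above 5%: 22.6% for five independent tests, about 18% at a correlation of 0.5, 15% at 0.7 and 10% at 0.9. By hypothesis it is 9–10% for H1 and 12.5–14% for H2 at correlations of 0–0.5. A T1/T2 split takes the total to at most about 30%, or about 23% at a common correlation of 0.5.

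These figures rest on two assumptions: that one significant scale is taken as support, and that the correlations lie in the range shown. The documents give neither, so 18–30% should not be read as a firm interval, and 18% is not a floor. The conclusion does not depend on the exact value: for the five scales together, every correlation tried gives at least twice the nominal level.

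The count leaves out the per-protocol repeat and the possible move to logistic or ordinal models.

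**What to change.** 1. **Step 4, significance rule.** Apply Holm across the five primary scales at an overall two-sided 0.05 (steps 0.01, 0.0125, 0.0167, 0.025, 0.05). Alternatively, name one lead scale per hypothesis, apply Holm across those two (0.025, then 0.05), and make the other three secondary.
2. **Step 1.1.** Replace the conditional split with one fixed primary follow-up contrast for EOLD-CAD and QOD-LTC, for example T1 and T2 combined, with T1-only and T2-only as secondary. Which contrast to fix is a design choice. What matters is that it is fixed and does not depend on a later power calculation.
3. **Primary outcome measures (clarification).** State that staff-rated EOLD-CAD is the primary version, in line with H1 and its sample, and that relative-rated EOLD-CAD is secondary.

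The change is to SAP wording only. The cost is power: a scale with 80% at 0.05 has about 71% at 0.025, and about 59% at 0.01, the strictest Holm step over five. Holm loses less once other scales have been rejected. Combining T1 and T2 can offset the loss only for the two resident scales, and only relative to a split analysis. The three staff scales have a single follow-up and gain nothing from it.

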## **SUB-ANALYSES**

The primary aim of the sub-analyses is to evaluate the effectiveness of the 'PACE Steps to Success' palliative care programme on different subgroups. For instance, the sub-analysis may aim to elucidate whether the effects of the 'PACE Steps to Success' palliative care programme on quality of dying of residents vary by characteristics of the deceased resident (i.e. age and gender, socio-economic status, clinical characteristics – e.g. cognitive status – dementia diagnosis –, and functional status). Each partner organization will create their own sub-analysis plan relevant to their research questions and hypotheses.

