### **Step 4. Conducting statistical analyses to test study hypotheses**

#### ***Intention-to-treat and per protocol analysis***

The primary statistical analyses will use the intention-to-treat (ITT) approach. With the ITT approach, the outcome data from all of the samples who were enrolled and randomized to the intervention group or the control group will be accounted for in the main analyses in the original groups to which they were randomized, regardless of whether or not they completed the PACE Steps to Success training. This approach may reflect the

effects of 'PACE Steps to Success' palliative programme on quality of dying of residents, staff attitudes and knowledge towards palliative care, and quality of palliative care in daily practice.

Per protocol analysis will also be performed. This includes LTCFs which were able to complete the study "according to the protocol". Based on the process evaluation measures, we will determine the cut offs to identify which LTCFs had followed the 'PACE Steps to Success' palliative care programme protocol. Per protocol approach may lower evidence level by introducing attrition bias because those who were only able to attend 2 of the 6 PACE trainings for instance may have different characteristics than those who attended all training sessions. Nonetheless, this approach better reflects the effects of 'PACE Steps to Success' palliative programme on quality of dying of residents, staff attitudes and knowledge towards palliative care, and quality of palliative care when intervention is implemented and taken in an optimal manner.

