### ***Regression analyses***

For this sub-analysis, several regression analyses will be conducted based on the exploration of data and data assumptions, as well as on the data analysis approach to be used (ITT and per protocol). Generally, the EOLD-CAD or QOD-LTC variables are by nature continuous variables, which would require multivariate linear regression analysis techniques. However, if the assumptions of normal distribution and/or linearity is/are violated, multivariate logistic regression analyses may be applicable. The specific procedure on how to further analyse skewed or non-linear data will rely upon the decision of the consortium. Basically, multivariate linear or logistic regression analyses may be performed to assess and compare the baseline and post-intervention measurement differences in the quality of dying between residents with and without dementia, both for the intervention group and the control group, while adjusting for sample characteristics that may differ between groups.

Additionally, multi-level mixed model regression analyses will be performed to account for the baseline measurement and the multilevel nature of the data – e.g. residents and staff nested within LTCFs or country. The kind of multilevel mixed model regression analyses will depend on the nature of the outcome variables and the statistical package to be used for the main analyses.

With the multi-level mixed model analyses, the outcomes will be analysed with LTCFs and country as random factor, and group, time point, and their interaction as fixed factors. Differences in mean change (post-intervention measurements minus baseline) between deceased residents with and without dementia, both for the intervention group and the control group (interaction group\*time\*dementia) will be calculated. Estimated means with corresponding 95% CI will be reported at baseline and follow-up, both for the intervention and control group. Moreover, estimated differences (and 95%CI) in change between intervention and control will be reported. The effect sizes (Cohen's *d*) using the baseline-adjusted mean differences and the variance between residents or care staffs, between LTCFs, and between country will be estimated to assess the magnitude of the effects for the different outcome measures.

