All analyses will be two-tailed and considered significant if  $\alpha = 0.05$ . In addition, data will be analysed by using statistical software program suitable for the necessary statistical analyses, such as multilevel mixed model analysis and multiple imputation – e.g. STATA, SAS, or IBM SPSS.

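### The SAP leaves subgroup tests to open-ended partner plans at two-sided 0.05 each, with no exploratory label, cap or adjustment, so the chance of a false subgroup finding is well above 5%

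*Combined protocol and SAP*

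**What the plan says.** All references are to Section I (Outcome evaluation plan) of the combined protocol and SAP.

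- **Aim.** The SUB-ANALYSES section says: "The primary aim of the sub-analyses is to evaluate the effectiveness of the 'PACE Steps to Success' palliative care programme on different subgroups". The opening of Section I also makes variation between subgroups part of the SAP's purpose.
- **Modifiers.** The characteristics named are "age and gender, socio-economic status, clinical characteristics – e.g. cognitive status – dementia diagnosis –, and functional status". They are introduced as examples: "For instance, the sub-analysis may aim to elucidate whether the effects of the". The list is therefore open.
- **Who decides.** "Each partner organization will create their own sub-analysis plan relevant to their research questions and hypotheses". The number of partners, plans or tests is not given, nor is a date by which those plans must be fixed.
- **Significance rule.** At the end of the main Regression analyses section, and again at the end of the dementia example: "All analyses will be two-tailed and considered significant if" alpha is 0.05.
- **Outcomes and analysis sets.** The dementia example concerns quality of dying, where "the EOLD-CAD or QOD-LTC variables are by nature continuous variables". SUB-GROUP DATA ANALYSIS refers back to the main SAP for the ITT and per-protocol approach, and there "Per protocol analysis will also be performed".
- **Time points.** Step 1.1 adds that "T1 and T2 can be used separately for the analysis when statistical power is at least 80" per cent.
- **Form of the test.** The dementia example uses a group by time by dementia interaction and reports estimated differences in change with 95% CIs.

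The SAP does not describe subgroup results as exploratory, limit their number, make them depend on the overall result, or adjust for multiplicity.

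**The concern.** The SAP supplies a decision rule, so this is more than a missing detail. A partner who follows it may report any subgroup effect with p<0.05 as a significant finding about effectiveness in that subgroup. Nobody has to disclose how many such tests were run across the consortium. When several modifiers are crossed with two scales and two analysis sets, the chance that at least one test crosses 0.05 rises well above 5% even if the programme works equally in all residents. A chance result of this kind could be read as showing that the programme suits, or does not suit, a group such as residents with dementia.

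**Working it through.** **Plan's own figure.** The SAP gives no family-wise error rate, count of subgroup tests or subgroup power. The only figure to reproduce is the per-test level: 1 − (1 − 0.05)^1 = 0.05.

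**Inputs from the documents**
- Two-sided 0.05 per test (Regression analyses; repeated in the dementia example).
- Five named modifiers: age, gender, socio-economic status, cognitive status/dementia, functional status (SUB-ANALYSES). It is six if cognitive status and dementia diagnosis are counted separately.
- Two quality-of-dying scales, EOLD-CAD and QOD-LTC.
- Two analysis sets, ITT and per protocol.

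**Assumptions**
- The number of tests, m. Five modifiers on one scale give m = 5; on two scales, 5 × 2 = 10; with per-protocol versions, 10 × 2 = 20. These counts are built from an illustrative list and are not commitments in the SAP.
- The correlations between test statistics.
- No true subgroup difference exists.

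**Independent tests**, 1 − 0.95^m:
- m = 5: 1 − 0.7738 = 22.6%
- m = 6: 26.5%
- m = 10: 1 − 0.5987 = 40.1%
- m = 20: 1 − 0.3585 = 64.2%
- The rate first passes 50% at m = 14 (51.2%).

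**Equally correlated tests.** Each statistic is z_i = √ρ·c + √(1 − ρ)·e_i, with c shared and e_i independent, and is counted as a false positive if |z_i| > 1.96. Simulation with 400,000 draws gives the chance of at least one false positive:

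| Tests | ρ = 0 | ρ = 0.5 | ρ = 0.8 |
|---|---|---|---|
| 5 | 23% | 18% | 13% |
| 10 | 40% | 29% | 17% |

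**Independent modifiers, two scales correlated 0.5.** Within one modifier, the chance that neither scale is significant is about 0.909. Over five modifiers: 1 − 0.909^5 ≈ 38%.

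**Adding per-protocol versions** (correlation 0.8 with the ITT statistic). Within one modifier, the chance that none of the four tests is significant is about 0.86. Over five modifiers: 1 − 0.86^5 ≈ 53%. At a correlation of 0.9 it is 49%. If instead all 20 tests share one common correlation of 0.5, it is 42%.

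**Not counted.** Modifiers that partners add, the other scales, and separate T1 and T2 analyses. Each would raise the figures.

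**If adjustment were used.** Bonferroni at m = 10 tests each effect at 0.05/10 = 0.005. For independent tests the family-wise rate is then 1 − 0.995^10 = 4.9%.

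**The case against.** The strongest case on the other side has five parts.

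- **The count is not the SAP's.** The list is illustrative, so 5, 10 or 20 tests is an assumption. This stands, and the result is therefore given as a range.
- **A false claim is not shown to be likely.** A reader might infer that a false subgroup claim is more likely than not. The documents do not support that: at 10 tests with correlation 0.5 the figure is 29%. Only the scenario with per-protocol versions passes 50%, and it treats them as separate claims although the SAP makes ITT primary and itself warns that the per-protocol approach may weaken the evidence.
- **The aim is not declared confirmatory, nor the partners uncoordinated.** A reader might infer both. The SAP says neither. Hypotheses 1 to 3 do not concern subgroups, and the partner plans, which are not available here, could contain limits or a stricter rule. What remains is that this SAP requires none.
- **The second statement of the 0.05 rule sits inside a worked example.** True, but the main Regression analyses section applies the same rule to all analyses, and SUB-GROUP DATA ANALYSIS presents its text as specifics for the sub-analyses generally.
- **The example already tests an interaction with CIs.** This is the right form of test and a strength of the plan. It guards against comparing separate within-subgroup p-values, but each interaction test at 0.05 keeps its own 5% error rate.

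Nor does any section say that subgroup results will decide who receives the programme, so the practical harm is a risk of misreading and not a planned consequence.

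**Conclusion.** The concern holds. As written, the SAP lets an unstated number of partner-planned subgroup tests each be called significant at two-sided 0.05, under an aim worded as effectiveness. With 5 to 10 tests the family-wise false-positive rate is about 13% to 40%, that is, 2.6 to 8 times the nominal 5% (13/5 and 40/5). It reaches about 53% only if modifiers are independent and per-protocol versions of 10 tests count as separate findings. These figures rest on assumed test counts and correlations; the direction does not, since running more than one test that is not perfectly correlated with the others raises the rate above 5%. The primary and secondary hypotheses are unaffected. What changes is how far a subgroup result may be believed.

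**What to change.** 1. In SUB-ANALYSES and at the end of the sub-group section, replace the 0.05 significance rule for sub-analyses. State that they are exploratory, that ITT leads, and that a nominal p<0.05 supports no claim of effectiveness in a subgroup. Make clear that the all-analyses sentence in the main SAP does not extend to them.
2. Report each sub-analysis as subgroup-specific effects plus the interaction estimate, with 95% CIs and the interaction p-value. The dementia example already goes most of the way.
3. Collect all partners' modifiers and outcomes in one list, fixed before post-intervention data are analysed, and state the number of interaction tests alongside each result.
4. If a subgroup is meant to be confirmatory, name it in advance on one scale. If there is more than one, apply Holm across them.

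The exploratory label does not lower the error rate; it limits what may be concluded. Only the Holm step controls the rate, and only for the subgroups it covers. The cost is a few sentences and a shared list, with no new data or sample size. The small downside is that partners can no longer call a nominal subgroup p<0.05 significant.
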